# GENERAL INFORMATION

## Trial registration

Chinese Clinical Trial Registry: http://www.chictr.org.cn

# SYNOPSIS

**Background**

The global increase in the aging population is escalating challenges in healthcare and society, particularly with the prevalence of sarcopenia. Sarcopenia, a condition marked by loss of skeletal muscle mass and function is rising among the elderly, affecting 10-27% and severely increasing mortality risks. Current palliative interventions focus on exercise and nutritional supplementation, with no optimal regimen identified for sarcopenia. High-intensity interval training (HIIT) has gained traction for its potential benefits over traditional moderate-intensity continuous training (MICT), showing promising results in improving muscle mass and exercise capacity in older adults, particularly in those with post-cardiac intervention. Despite the advantages of HIIT in stimulating skeletal muscle and increasing protein synthesis, research comparing its effects to MICT on sarcopenia and the key sensors at play is scant.

**Aim of the trial:** This trial is to explore the differentially expressed plasma proteins induced by high-intensity interval training and moderate-intensity continuous training using omics technologies and bioinformatics methods.

**Type of the trial:** Randomized crossover trial.

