**Evaluation and visit schedule**

**Table 1. Summary of examinations at different time-points**

| **Study Visits** | **MICT-first group** | **HIIT-first group** |
| --- | --- | --- |
| Screening (at the begining) | Medical history, physical activity habit assessment, anthropometric measurements. | |
| Visit 1 (2^nd^ week) | Cardiopulmonary exercise testing, resting ECG | |
| *Randomization* | | |
| Visit 2 (4^th^ week) | First time exercise: Venous blood will be drawn for non-specific proteomic analysis 5 minutes before exercise and 15 minutes after exercise. | |
| *Two weeks of washout period.* | | |
| Visit 3 (6^th^ week) | Second time exercise: Venous blood will be drawn for non-specific proteomic analysis 5 minutes before exercise and 15 minutes after exercise. | |

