Previous research on the mechanisms of exercise has largely centered on understanding how exercise affects specific molecules or pathways, constrained by the available research methodologies. Prior findings have demonstrated that exercise can positively influence mitochondrial quality control in both skeletal and cardiac muscles of mice. This is achieved through the activation of AMPK, which leads to improvements in insulin resistance and an enhancement in stress resistance. [8-12]. Recently, the development of multi-omics technologies and bioinformatics has provided methods to explore comprehensive exercise responses. Using these methods, researchers like Contrepois [13] and Whitham [14] have reported the acute molecular responses of healthy adults to a single session of moderate-intensity exercise. In their studies, during a single session of moderate-intensity exercise thousands of molecular changes and biological processes were revealed, including energy metabolism, oxidative stress, inflammatory responses, tissue repair, growth factor responses, and regulatory pathways. The comprehensive proteomic characteristics between different exercise intensities are not yet clear and have not been reported.

This study intends to use a crossover trial design, employing non-specific proteomics techniques and bioinformatics methods to map the molecular responses of adult plasma to MICT and HIIT. This research will be the first to explore proteins specifically and co-expressed in both forms of exercise, providing data support and direction for subsequent research in precise exercise therapy; it will also provide information for the development of exercise mimetics, allowing patients who are unable to participate in exercise due to functional impairments to also gain the health benefits associated with exercise.

**We hypothesize** that the HIIT will induce a distinctive plasma protein response in contrast to MICT.

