## Objectives

**Primary Objective**

To delineate the proteomic responses in adult plasma following MICT and HIIT.

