## Statistical methods

The Shapiro–Wilk test will be performed to determine normality for continuous variables. Descriptive statistics will be presented as mean ± SD for normally distributed continuous variables while those with a non-normal distribution as median interquartile range (IQR)..

In this study, proteomic data will be processed using Spectronaut Pulsar, with raw data files converted to a standard format by local normalization. The data will undergo pre-processing to remove low-quality spectra and to normalize signal intensities across samples. Peptide identification will be performed using the UniProt with a false discovery rate (FDR) of 0.01 to control for type I errors. Quantitative data analysis will be conducted using R, where peptide intensities will be compared across samples using *t*-test. Differential expression analysis will be performed to identify significantly regulated proteins, with a *P*-value < 0.05 and foldchange threshold of 1.2 considered statistically significant. Venn analysis will be applied to visualize shared and unique proteins between MICT and HIIT.

When comparing two group means, *t*-test will be used in an unpaired two-tailed fashion. For more than two groups, ANOVA with Bonferroni multiple comparisons test will be used. Adjusted Pearson correlation analysis will be used to assess the association between two factors. All analyses were performed using R (version 4.2.0) software. Statistical significance was set at *P*<0.05 (two-sided).

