## Assignment and allocation of intervention

After informed consent and screening, participants will be randomised (1:1) to the MICT-first group and HIIT-first groups.

**Sequence generation:** For allocation of participants, an investigator with no involvement in the intervention part of the trial will prepare a computer-generated list of random numbers that will be used to assign participants in a 1:1 ratio to the MICT-first and HIIT-first groups.

**Concealment mechanism:** The allocation sequence will be concealed from the researcher enrolling and assessing participants in sequentially numbered, opaque, sealed, and stapled envelopes.

**Implementation:** After acceptance of a participant by the panel, and before admission to a group, the appropriate numbered envelope will be opened; the card inside will inform if the participant is to be assigned to the MICT-first or the HIIT-first group, and this information will then be given to the researchers responsible for intervention.

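### With no resting session, protein changes common to HIIT and MICT cannot be attributed to exercise; only the HIIT-minus-MICT difference in change is randomised

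*Protocol*

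**What the plan says.** The aim in the Synopsis is to explore "differentially expressed plasma proteins induced by high-intensity interval training and moderate-intensity continuous training". Section 3.1 adds: "This research will be the first to explore proteins specifically and co-expressed in both forms of exercise". It then says of the research that "it will also provide information for the development of exercise mimetics". The primary objective in section 3.2 is "To delineate the proteomic responses in adult plasma following MICT and HIIT".

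In section 4.7 the shared and mode-only lists come from an overlap step: "Venn analysis will be applied to visualize shared and unique proteins between MICT and HIIT". A protein counts as regulated at P below 0.05 with a fold change of 1.2. The section does not say which two sets of samples are compared to form each mode's list.

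On design, section 4.10 says "participants will be randomised (1:1) to the MICT-first group and HIIT-first groups". Table 1 gives the sampling at each exercise visit: "Venous blood will be drawn for non-specific proteomic analysis 5 minutes before exercise and 15 minutes after exercise". The Blood collection text in section 5 counts four draws per man, all before or after an exercise session. Neither Table 1 nor Table 2 contains a resting session.

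**The concern.** A crossover that randomises the order of two exercise modes gives a randomised comparison of one mode with the other. It gives none of exercise with no exercise. Each mode's own change from before to after is an uncontrolled before-after comparison, and the post-session sample always comes second.

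Anything protein-specific that shifts over that hour for reasons other than exercise (time of day, a repeat venepuncture, sample handling) is present in both sessions. It cancels when the two changes are subtracted. It does not cancel within a mode, and because it recurs in both modes it falls in the overlap.

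The overlap is a planned product of the trial, and the aim gives it a causal label. A reader could take non-exercise drift for a common exercise signature. Testing the overlap more carefully would not help, because the missing element is a comparator.

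**Working it through.** **1. Time between samples.** From Table 1 and section 4.5: 5 min before + 41 min session + 15 min after = 61 min. Both modes total 41 min, so the gap is the same in each.

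**2. What cancels.** Let a protein's mean change be e(mode) + g, where e is the exercise effect and g the non-exercise drift over the hour.
- HIIT change minus MICT change: e(HIIT) + g − e(MICT) − g = e(HIIT) − e(MICT). The drift drops out, and randomised order balances any period difference on average.
- HIIT change alone: e(HIIT) + g. MICT change alone: e(MICT) + g. With no exercise effect, both equal g.

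**3. The plan's own figure.** Section 4.4 gives 8 evaluable and 10 enrolled, from a difference of 21.9, SD 15.0, alpha 0.05 and power 0.80. Reading 15.0 as a within-person SD, normal approximation: 2 × [15.0 × (1.960 + 0.842) / 21.9]² = 7.36, rounded up to 8; 8 / 0.8 = 10. This sizes the HIIT-versus-MICT comparison and is not in dispute. I use n = 10 below.

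**4. Illustration: no exercise effect, the same drift in both sessions.** Assumptions not in the protocol:
- drift of d = 0.5, 1.0 or 1.5 SD of the within-person change;
- within-person CV of 15% to 25% per sample;
- between-person SD of 0.5 on the log2 scale.

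The within-person log2 SD per sample is √ln(1 + CV²) / ln 2, which is 0.215 (CV 15%) and 0.355 (CV 25%). Multiplying by √2 gives the SD of the change: 0.304 and 0.502. The drift as a fold change is 2^(d × SD of change).

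First, a paired test at two-sided 0.05 with no fold-change filter. Power from the non-central t (9 df, non-centrality d√10) is 0.293, 0.803 and 0.987. Squared for presence in both lists, this gives 0.086, 0.645 and 0.975.

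Next, by simulation, with the section 4.7 rule (P < 0.05 and at least 1.2-fold) met in both sessions:

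| d | Fold drift, CV 15% / 25% | Shared, paired test | Shared, unpaired test | HIIT-minus-MICT change, P < 0.05 |
|---|---|---|---|---|
| 0.5 | 1.11 / 1.19 | 1% / 8% | 0.03% / 0.5% | about 5% |
| 1.0 | 1.23 / 1.42 | 42% / 64% | 2% / 17% | about 5% |
| 1.5 | 1.37 / 1.69 | 95% / 98% | 22% / 71% | about 5% |

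Repeat runs move these by up to about one percentage point. The unpaired column is shown because section 4.7 specifies an unpaired test when two group means are compared. The last column is a within-person test of the difference in change. With no drift at all, a protein is called shared at most about 0.2% of the time under either test.

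**The case against.** The case against is substantial, and much of it stands.

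- **The drift is hypothetical.** A reader might infer that time and sampling effects would be reported as exercise proteins. The protocol does not support that. It gives no size for any drift, and a drift must pass both criteria in both sessions to be listed. The supportable statement is that such a drift could not be told apart from a shared response.
- **The contrast is inferred.** Section 4.7 does not name a before-after comparison. The paired draws, the objective and the overlap step point to one, but it is not written down.
- **The unfiltered paired figures overstate the risk.** They ignore the fold-change rule and the unpaired test in section 4.7. With both applied, the chance is small at d = 0.5 and 1.0 when CV is 15%, and is substantial only for larger drifts.
- **Part of the drift is removed.** Equal protein loading (Protein digestion) and cross-run normalisation (Database search) would largely remove a uniform shift, such as one from posture or plasma volume. Protein-specific changes remain.
- **The wording is mostly cautious.** Sections 3.2 and 4.6 already describe what follows or is observed after exercise. Among the aim, objective and outcome statements, only the aim uses causal language.
- **Mimetics.** A reader might infer that the shared proteins in particular are offered as the basis for mimetics. Section 3.1 ties that sentence to the research as a whole.
- **The main hypothesis is unaffected.** It concerns HIIT against MICT, as does the sample size, and section 4.4 calls the study exploratory.

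The exploratory label limits the consequence but does not justify describing uncontrolled changes as induced by exercise. Nor does the sentence in section 6.3 about randomising to exercise or an advice-only control group supply a comparator. It has no counterpart in the schedule or the randomisation and must be reconciled with them.

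**Conclusion.** The point holds at low severity. Only the HIIT-minus-MICT difference in change rests on randomisation. The per-mode and shared lists, if formed from before-after comparisons, cannot separate exercise from other changes over about 61 minutes.

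The size depends on unknowns. Across the assumed drifts and variabilities, the chance of a false shared label runs from about 1% to 98% with a paired test and from about 0.03% to 71% with an unpaired one, against about 5% for the randomised contrast. These figures show what the design cannot rule out. They do not predict what the trial will find.

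A reader might also conclude that the trial needs a resting session or that its main comparison is compromised. Neither follows: the between-mode hypothesis stands, and the problem is how far the conclusions reach.

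**What to change.** Change wording only:

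1. In the Synopsis aim, replace the causal verb with wording such as *changed after*. Reserve causal attribution for the randomised HIIT-minus-MICT difference in pre-to-post change.
2. In sections 3.1 and 4.7, state that the per-mode and shared lists are uncontrolled pre-to-post changes without a resting comparator, and are hypothesis-generating.
3. Qualify the mimetics sentence in section 3.1 in the same way. It need not be deleted.

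Sections 3.2 and 4.6 need no edit for this point. No added session, participant or assay is required. The cost is a weaker claim for the shared proteins.

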**Participants**

**Inclusion criteria**

- Sedentary males aged 30-35 years;
- Generally in good health condition;
- Able to comply with and complete the exercise cardiopulmonary test evaluation;
- Willing and consents to participate in the study.
- Sedentary lifestyle in the past three months: sedentary is defined as individuals who exercise less than 3 hours per week and have more than 8 hours of static activity daily. Static activity time refers to the total time spent on activities such as using a computer, writing materials, attending meetings during work, and watching TV, playing computer games, playing chess, reading, etc., after work. Weekly exercise time refers to the total time the participant engages in fitness exercises of moderate intensity (slightly strenuous) or above each week.

**Exclusion criteria**

- Have musculoskeletal functional impairments that affect participation in exercise;
- Suffer from uncontrolled diseases;
- Have taken drugs that affect metabolism or cardiovascular response in the past two weeks;
- Have participated in systematic exercise training;
- Have dieted or attempted to lose weight in the past two weeks;
- Are currently participating in other clinical trials;
- Cannot confirm the ability to complete the study due to personal life arrangements, such as having plans for long-distance travel.

**Dropout criteria**

- The patient cannot tolerate the designated intensity of exercise training during the study;
- Serious safety issues arise during the trial;
- The patient develops new illnesses;
- There are significant changes in the patient's lifestyle and dietary habits during the trial;
- The researcher believes that further trials are not in the best interest of the participant;
- The patient revokes informed consent.

**Number of subjects:** N = 10

**Primary outcome:** Proteomic responses in plasma following MICT and HIIT

**Type of intervention** Exercise training

**Intervention protocols:**

**(1) MICT:** The MICT protocol consists of a 1-minute warm-up, followed by training at 50% maximum exercise capacity for 36 minutes, and concluding with a 4-minute cooldown, resulting in a total exercise duration of 41 minutes.

**(2) HIIT:** HIIT involves a 5-minute warm-up, followed by four repetitions of high-intensity training and a low-intensity recovery cycle, and ends with a 4-minute cooldown, also totaling 41 minutes. Each cycle of HIIT includes 4 minutes of high-intensity training at 70% maximum exercise capacity, followed by 4 minutes of low-intensity training at 30% maximum exercise capacity.

**Time plan:** Start: May 2023

First inclusion of participants: May 2023

Inclusion of all participants: Dependent

All participants completed the study: Dependent

**Statistical analysis:** The proteomic data will be analysed by an expert who is good at bioinformatics.

**
[figure not shown]
Flow chart**

**Evaluation and visit schedule**

**Table 1. Summary of examinations at different time-points**

| **Study Visits** | **MICT-first group** | **HIIT-first group** |
| --- | --- | --- |
| Screening (at the begining) | Medical history, physical activity habit assessment, anthropometric measurements. | |
| Visit 1 (2^nd^ week) | Cardiopulmonary exercise testing, resting ECG | |
| *Randomization* | | |
| Visit 2 (4^th^ week) | First time exercise: Venous blood will be drawn for non-specific proteomic analysis 5 minutes before exercise and 15 minutes after exercise. | |
| *Two weeks of washout period.* | | |
| Visit 3 (6^th^ week) | Second time exercise: Venous blood will be drawn for non-specific proteomic analysis 5 minutes before exercise and 15 minutes after exercise. | |

# INTRODUCTION

## 3.1 Rationale

A substantial body of research has shown that regular exercise can significantly improve the physiological functions of multiple organs and systems, reducing the incidence of cardiovascular diseases and the risk of all-cause mortality, and promoting heathy aging [1, 2]. Just like a drug prescription, an individualized exercise prescription is fundamental in promoting health benefits related to exercise and implementing precise treatments for participants. An exercise prescription mainly comprises factors like the mode of exercise, intensity, duration, and frequency [3]. Exercise intensity might be a key modulating factor, as the health benefits of 75 minutes of high-intensity exercise are similar to those produced by 150 minutes of moderate-intensity exercise per week [1, 4, 5]. Another research also indicates that HIIT for the same duration is more effective than MICT in improving metabolic syndrome and body composition in patients post-percutaneous coronary intervention [6, 7]. The differences in molecular responses induced by exercises of varying intensities are not yet clear. Exploring the molecular sensors and regulatory mechanisms of different exercise intensities can aid in advancing precise exercise therapy and provide a basis for the development of exercise mimetics.

Previous research on the mechanisms of exercise has largely centered on understanding how exercise affects specific molecules or pathways, constrained by the available research methodologies. Prior findings have demonstrated that exercise can positively influence mitochondrial quality control in both skeletal and cardiac muscles of mice. This is achieved through the activation of AMPK, which leads to improvements in insulin resistance and an enhancement in stress resistance. [8-12]. Recently, the development of multi-omics technologies and bioinformatics has provided methods to explore comprehensive exercise responses. Using these methods, researchers like Contrepois [13] and Whitham [14] have reported the acute molecular responses of healthy adults to a single session of moderate-intensity exercise. In their studies, during a single session of moderate-intensity exercise thousands of molecular changes and biological processes were revealed, including energy metabolism, oxidative stress, inflammatory responses, tissue repair, growth factor responses, and regulatory pathways. The comprehensive proteomic characteristics between different exercise intensities are not yet clear and have not been reported.

This study intends to use a crossover trial design, employing non-specific proteomics techniques and bioinformatics methods to map the molecular responses of adult plasma to MICT and HIIT. This research will be the first to explore proteins specifically and co-expressed in both forms of exercise, providing data support and direction for subsequent research in precise exercise therapy; it will also provide information for the development of exercise mimetics, allowing patients who are unable to participate in exercise due to functional impairments to also gain the health benefits associated with exercise.

**We hypothesize** that the HIIT will induce a distinctive plasma protein response in contrast to MICT.

## Objectives

**Primary Objective**

To delineate the proteomic responses in adult plasma following MICT and HIIT.

# METHODS

## Trial design

This is an open-label, randomised crossover trial.

## Setting

Xiangya Hospital, Central South University, Changsha, China.

## Selection of trial participants

**Inclusion criteria**

Participants must meet ALL of the following criteria:

1. Sedentary males aged 30-35 years;
2. Generally in good health condition;
3. Able to comply with and complete the exercise cardiopulmonary test evaluation;
4. Willing and consents to participate in the study.
5. Sedentary lifestyle in the past three months: sedentary is defined as individuals who exercise less than 3 hours per week and have more than 8 hours of static activity daily. Static activity time refers to the total time spent on activities such as using a computer, writing materials, attending meetings during work, and watching TV, playing computer games, playing chess, reading, etc., after work. Weekly exercise time refers to the total time the participant engages in fitness exercises of moderate intensity (slightly strenuous) or above each week.

**Exclusion criteria**

Participants will be excluded for ANY ONE of the following reasons:

1. Have musculoskeletal functional impairments that affect participation in exercise;
2. Suffer from uncontrolled diseases;
3. Have taken drugs that affect metabolism or cardiovascular response in the past two weeks;
4. Have participated in systematic exercise training;
5. Have dieted or attempted to lose weight in the past two weeks;
6. Are currently participating in other clinical trials;
7. Cannot confirm the ability to complete the study due to personal life arrangements, such as having plans for long-distance travel.

